## Abstract

**Background**:
Prenatal growth retardation may increase the risk of later chronic non-communicable diseases (NCDs), including diabetes; however, long-term effects of wasting malnutrition in childhood or adulthood are less studied. Pancreatic exocrine and endocrine functions, both critical for nutrition and NCD aetiology, may not fully recover following malnutrition. However, the evidence and mechanistic information is piecemeal. We hypothesise that wasting malnutrition at any age has long-term detrimental effects on endocrine and exocrine pancreatic structure and function.

**Methods: **The SAMPA international research programme will assess pancreatic structure and function in 3700 participants from ongoing observational nutrition cohorts, two adolescent and four adult, in Zambia, Tanzania, Philippines, and India. Pancreas size, structure, and calcification will be assessed by ultrasound and computed tomography (CT) scan; exocrine function by faecal elastase and serum lipase; and endocrine function by haemoglobin A1c (HbA1c) and blood glucose, insulin and C-peptide concentrations during an oral glucose tolerance test (OGTT). In-depth hormonal analyses of incretins, glucagon, proinsulin and trypsinogen during OGTT and intravenous glucose tolerance tests will be done in subsets of adult participants. Pancreatic size and function outcomes will be compared between people with and without prior wasting malnutrition. Analyses will investigate effect modification by sex, current age, time since malnutrition, current body mass index and dietary patterns. Mathematical modelling of OGTT data will be used to estimate the relative contribution to glucose dysregulation of decreased insulin production, changes in insulin clearance and increased insulin resistance. Proinsulin/insulin ratio will be analysed in archived samples from the Tanzanian cohort using a nested case-control design to investigate whether abnormal values precede diabetes.

**Conclusions:** SAMPA, a large-scale multi-centre research programme using data from people with or without prior wasting malnutrition to assess several aspects of pancreatic phenotype, will provide coherent evidence for future policies and programmes for malnutrition and diabetes.

## Introduction

There is an increasing prevalence of overweight and obesity worldwide which is associated with increases in non-communicable diseases (NCDs), including diabetes.
^
1
^ Meanwhile, wasting malnutrition remains common in low- and middle-income countries (LMICs).
^
2
^ It is well-documented that prenatal malnutrition, usually measured as low birth weight, can increase the risk of NCDs in later life,
^
3
^ but how wasting malnutrition in childhood or adulthood may affect long-term health is less studied.
^
4
^ The issue of child or adult malnutrition's long-term implications is becoming increasingly important because more children survive severe acute malnutrition as a result of improved care, while pharmacological treatments for infections, such as HIV and tuberculosis, that commonly cause or are linked with malnutrition, have increased patient survival among all age groups. Evidence from a recent systematic review suggests pancreatic endocrine and exocrine functions may not recover fully after childhood or adult wasting malnutrition.
^
5
^ Such long-term effects on the pancreas may contribute to the different phenotype of diabetes common in LMICs with prevalent malnutrition, compared with the diabetes phenotype in high-income countries. Diabetes in LMICs often has a relatively early disease onset (<50 years) and may occur at a low or normal body mass index (BMI).
^
6
^ There are heterogeneous reports of atypical diabetes in LMICs, describing an entity of malnutrition-related, insulin-deficient diabetes related to pancreatic damage, for example, a phenotype termed fibrocalculous pancreatic diabetes,
^
7
^ but these studies often report highly selected patients, which can provide mechanistic but not epidemiologic information,
^
8
^ or precede the availability of modern assessment methods.
^
9
^ Our own work has shown that prior malnutrition in Tanzanian adults is associated with lower insulin production in men
^
10
^ and that insulin deficiency is a more common cause of diabetes than insulin resistance.
^
11
^ If malnutrition is associated with an atypical form of diabetes, driven by insulin deficiency and not resistance, then this has major implications for health policy, planning, investigation and treatment of diabetes in LMICs, because current first-line treatments of diabetes in these settings usually use treatments such as metformin which would be inappropriate for insulin-deficient diabetes.

Both pancreatic endocrine (
*i.e.* production of hormones such as insulin) and exocrine (
*i.e.* production of enzymes to aid digestion) functions are critical for nutritional metabolism and in chronic diseases including diabetes. Furthermore, deficits in exocrine and endocrine functions may interact such that diabetes is common among people with exocrine pancreas insufficiency
^
12
^ and low faecal elastase is common in patients with type 2 diabetes, especially those with poor glycaemic control.
^
13
^ There is a dearth of studies explaining the mechanisms of the exocrine-endocrine interactions leading to abnormalities in both functions.

In spite of its central importance, there has been surprisingly little research on pancreatic function following recovery from wasting malnutrition. This is likely due, in part, to there being no validated, easily measurable indicator of prior wasting malnutrition, in contrast to studies of poor early linear growth, resulting in largely irreversible stunting, short legs, and increased sitting/standing height ratio in adulthood. There is thus an urgent need for prospective cohort studies to investigate long-term effects of wasting malnutrition.

The central hypothesis of the severe acute malnutrition in children and adults - the role of the pancreas (SAMPA) study is that an episode of wasting malnutrition, irrespective of age of occurrence, affects endocrine and exocrine pancreatic size, structure and function. The study will recall for cross-sectional investigations participants from established cohorts recruited for the research team’s previous studies in Tanzania, Zambia, India and the Philippines. Many cohort members were originally recruited because of an episode of severe malnutrition or their infection with HIV or tuberculosis; their prior nutritional status, plus those of well-nourished controls, is documented. The cohorts now range in age from adolescence to late middle age and live in places with a wide range of access to foods high in fat and sugar which, combined with a more sedentary lifestyle, could affect their risk of diabetes. We will assess the association of prior wasting malnutrition with current pancreas structure and function, taking into account factors such as sex, current age, time since malnutrition, current BMI and body composition, and infections which could affect pancreas functions.
Figure 1 shows the conceptual framework guiding the programme of research.

**Figure 1. f1:**
[figure not shown]
Conceptual framework linking wasting malnutrition with later impaired endocrine and exocrine pancreas function.

The above relationships may be subject to modification by sex, age at pancreas assessment, time since malnutrition, BMI, diet, or HIV status.

## Protocol

### Study objectives and hypotheses

*Overall hypothesis*

Wasting malnutrition at any age has medium- and long-term detrimental effects on endocrine and exocrine pancreatic function and structure.
1.
**
*Specific objective 1*:** To investigate whether wasting malnutrition at various ages is associated with abnormalities of pancreas structure and function later in life.a.
**
*Hypothesis 1*:** Prior wasting malnutrition is associated with later abnormal pancreatic structure and endocrine and exocrine function.b.
**
*Pancreatic phenotype of interest:*
** Diabetes assessed by oral glucose tolerance test (OGTT) and haemoglobin A1c (HbA1c), exocrine pancreatic function tests (serum lipase, faecal elastase), pancreatic size and architecture measured using ultrasound for all participants and measured using computed tomography (CT) scans for a subset of participants (non-pregnant adult participants).2.
**
*Specific objective 2:*
** To investigate whether pancreatic abnormalities in participants with prior malnutrition and diabetes are analogous to a previously described entity of fibro-calculous diabetes.a.
**
*Hypothesis 2:*
** Prior wasting malnutrition is associated with pancreatic calcification which in turn is associated with diabetes.b.
**
*Pancreatic phenotype of interest:*
** Pancreatic calcifications determined from CT scans among non-pregnant adult study participants.3.
**
*Specific objective 3:*
** To investigate the relative importance of decreased insulin production or increased insulin resistance in malnutrition-associated diabetes.a.
**
*Hypothesis 3:*
** The abnormal glucose regulation seen after wasting malnutrition is associated with relative insulin deficiency with or without insulin resistance.b.
**
*Pancreatic phenotype of interest:*
** Indices of glucose metabolism and insulin kinetics based on mathematical models of glucose and hormone concentrations during OGTT and intravenous glucose tolerance tests (IVGTT). Homeostasis model assessment of insulin resistance (HOMA-IR) and liver fat (insulin resistance) will also be assessed.4.
**
*Specific objective 4:*
** To investigate whether a prior abnormal pro-insulin/insulin ratio is associated with diabetes in adults infected or not with HIV or previously with tuberculosis.a.
**
*Hypothesis 4:*
** An abnormal pro-insulin/insulin ratio is associated with later development of diabetes in adults who had malnutrition earlier in life in association with HIV or tuberculosis infection.b.
**
*Pancreatic phenotype of interest:*
** Fasting proinsulin/insulin ratio among Chronic Infections, Co-morbidities and Diabetes in Africa (CICADA) cohort participants measured several years before the SAMPA investigations.

### Study cohorts

This study brings together diverse cohorts (
Table 1) under a common theme providing participants with prospectively assessed and clearly defined malnutrition exposure across populations and life-course and not previously malnourished controls, all from LMICs at various stages of the nutrition transition but with ongoing burden of infectious disease. Flow charts for each cohort are given in
Figures 2–
7.

**Table 1. T1:** Study cohorts for Severe Acute Malnutrition in children and adults - the role of the Pancreas (SAMPA).

	Cohort	Sample size-previous and expected
**1.**	** *DIVIDS (Delhi Infant Vitamin D Supplementation) study, India* ** The DIVIDS cohort comprises infants born low birth weight (LBW, <2.5 kg) at term in 2007-2010. They had monthly follow-up until 6 months ^ 14 ^ then at 5 years ^ 15 ^ and are currently, aged ~13 years. *For SAMPA, the DIVIDS cohort acts as a positive control since we expect adverse long-term non-communicable disease consequences of being born LBW.*	• Birth: 2079 total, all LBW • Age 5 y: 912 total, 764 (84%) BMIZ>-2, 138 (15%) BMIZ -2 to -3, 9 (1%) BMIZ<-3; 1 no anthropometry • Age ~13 y (ongoing): 647 total, 482 (75%) BMIZ>-2, 117 (18%) BMIZ -2 to -3, 48 (7%) BMIZ<-3 • Expected for SAMPA: 750 total
**2.**	** *SAM (Severe Acute Malnutrition), Lusaka, Zambia* ** This group comprises: a) 100 children who were hospitalised with malnutrition at University Teaching Hospital (UTH) between 2010 and 2014 when they were < 2 years b) 85 never-malnourished neighbourhood controls. Children were aged ~9 years at previous follow-up ^ 16 ^ and will be ~12 years for SAMPA.	• Age < 2 y: 100 malnutrition • Age 9 y: 185 total, 100 previous malnutrition, 85 no malnutrition; currently 17 (9%) BMIZ <-2 • Expected for SAMPA: 180 total
**3.**	** *CICADA (Chronic Infections, Co-morbidities and Diabetes in Africa), Mwanza, Tanzania* ** The CICADA cohort, ^ 17 ^ total n=1947, comprises three subgroups: a) Tuberculosis patients and controls from the TB-NUT study whose HIV and nutritional status ~16 years ago at recruitment are known (50% BMI<18.5 kg/m ^2^) as well as more recently recruited HIV-infected and uninfected people (controls) ^ 18 ^ ^,^ ^ 19 ^ b) NUSTART, conducted 2010-2014, was a two-site (Mwanza and Lusaka) trial of food supplements for malnourished (BMI<18.5 kg/m ^2^) HIV-infected adults, recruited when starting antiretroviral therapy. ^ 20 ^ In Mwanza, 704 participants were recruited, 409 were alive and followed at the 12-week NUSTART end-point; 273 were available at a follow-up two-three years after starting ART and 206 were recruited to the CICADA study. c) HIV-infected and uninfected people, both malnourished and well-nourished, recruited 3-four years ago for HIV, nutrition and diabetes assessments *CICADA has the most detailed longitudinal diabetes data of the project cohorts, archived fasting samples, and are the oldest so have had longer to develop diabetes; therefore, this cohort will be used for the in-depth and longitudinal components.*	CICADA (TB-NUT) 16 y prior: 450 total • 73 (16.2%) BMI <17 kg/m ^2^ • 74 (16.4%) BMI 17 to 18.5 kg/m ^2^ • 303 (67.4%) BMI > 18.5 kg/m ^2^ CICADA (NUSTART) 11 y prior: 208 total • 105 (50.5%) BMI <17 kg/m ^2^ • 103 (49.5 %) BMI 17 to 18.5 kg/m ^2^ CICADA (New HIV +/- cohort) 4 y prior: 1293 total • 109 (8.4%) BMI <17 kg/m ^2^ • 171 (13.3 %) BMI 17 to 18.5 kg/m ^2^ • 1009 (78.3%) BMI >18.5 kg/m ^2^ Expected for SAMPA: 1412 total
**4.**	** *NUSTART, Lusaka, Zambia* ** 200 previously malnourished HIV-infected adults will be traced and recruited from the NUSTART Lusaka participants. ^ 20 ^ We will also recruit 50 HIV-infected and 50 non-HIV-infected, not previously malnourished, neighbourhood controls.	• 10 y prior: 1111 total, 437 (39%) BMI 17 to 18.5 kg/m ^2^, 674 (61%) BMI<17 kg/m ^2^ • Expected for SAMPA: 300 total
**5.**	** *St-ATT (Starting Anti-TB Treatment) Cohort, Philippines* ** Between Aug 2018 and Feb 2020, the St-ATT cohort recruited 900 adults undergoing tuberculosis treatment in three provinces: Cebu, Negros Occidental and Metro Manila, encompassing urban, peri-urban and rural populations. 17% had HbA1c >=7.0% (probable diabetes in TB) with an additional 30% with HbA1c 5.8%-7.0% (‘prediabetes’/mild TB-induced hyperglycaemia). ^ 21 ^ https://www.isrctn.com/ISRCTN16347615 *This cohort will be involved in the in-depth analyses.*	• 1-2 y prior: 900 total, 495 BMI >18.5 kg/m ^2^, 189 (21%) BMI 17.0-18.5 kg/m ^2^, 216 (24%) BMI <17 kg/m ^2^ • Expected for SAMPA: 600 total
**6.**	** *CLHNS (Cebu Longitudinal Health and Nutrition Survey), Philippines* ** The mothers of the cohort were randomly selected in 1983-84 when they were pregnant. ^ 22 ^ All singleton births were included regardless of nutrition status. Since the original bimonthly follow-up surveys up to age two years, there have been 8 follow-up surveys including in 2018-2019 when 1326, ~43% of the initial birth cohort (3,080), were available. *This cohort represents our longest follow-up of malnutrition diagnosed by anthropometry.* (Earlier cohort data are available open access: https://www.cpc.unc.edu/projects/cebu).	• Birth: 28 LBW of the 143 with childhood malnutrition • Age ≤ 2 y: of 420 total to be included, 143 (34%) WHZ<-3 • Expected for SAMPA: 420 total

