### Assessments

The following assessments will be carried out on all consenting participants across the cohorts. Target sample sizes are as in
Table 1.
1.
**
*OGTT:*
** The primary outcome for comparing those with and without prior malnutrition across all cohorts will be glucose ≥ 7.8 mmol/L at 2 hours in a standard OGTT with 75 g glucose (in children, 1.75 g/kg body weight up to 75 g) that is, diabetes plus impaired glucose tolerance by WHO criteria.
^
23
^ Glucose in one hour samples in all participants will also be measured since this may be a better predictor of progression to diabetes due to insulin deficiency than the two-hour time point.
^
24
^ Those with OGTT compatible with diabetes will be called back for a repeat OGTT in order to determine need for referral for clinical care. Urine dipstick will also be done for ketones to assess potential need for (short-/long-term) insulin replacement therapy. Indices of beta-cell function, insulin kinetics, and insulin resistance will be modelled from glucose, insulin and C-peptide during OGTT.
^
25
^
^,^
^
26
^ Proinsulin will be measured in baseline samples only. Autoantibodies will be measured in participants with OGTT indicative of diabetes to confirm/exclude autoimmune type-1 diabetes.2.
**
*HbA1c*
**: This will be by point-of-care test (Hemocue, Angelholm, Sweden) using fingerprick blood samples for most cohorts to indicate long-term glycaemic control; for the DIVIDS cohort, HbA1c will be measured in venous blood by a commercial lab ([name] Labs, Delhi).3.
**
*Abdominal ultrasound*:** Ultrasound scans will be performed by trained sonographers or radiologists in identified health facilities. The participant will be asked to lie on the ultrasound examination bed. They will be asked to breathe in and hold their breath in order to optimise visualization of the pancreas. A curvilinear ultrasound probe (2-5 MHz) will be placed onto the participant’s abdominal wall in the upper abdomen to image the pancreas. Images of the pancreas will be recorded and saved. Parameters obtained from the scans will be pancreas size, duct size, calcification, or other abnormality.4.
**
*Exocrine pancreas markers:*
** These will be serum lipase in baseline OGTT samples and faecal elastase: Participants will collect faecal samples either in the clinic or bring them from home.5.
**
*Urine glucose and ketones by dipstick*
**: These will be from random urine collection.6.
**

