### Statistical analyses and sample size calculations

Analyses related to individual hypotheses are described below. Primary analyses will be conducted for each cohort separately. Pooled analyses using all or some cohorts combined will be conducted based on the individual cohort results, and in order to investigate how age at malnutrition and length of time between malnutrition and outcome assessment influence the associations between malnutrition and pancreas structure and function. Analyses will be guided by the conceptual framework in
Figure 1. Sample sizes for the specific hypotheses indicate that, with the available number of participants in the cohorts, we have sufficient power for the main analyses with all participants. For some expensive or labour- and participant-intensive outcomes, we had to consider cost and feasibility and have calculated power for analyses in subsets.

*Hypothesis 1:*
Prior malnutrition is associated with later abnormal pancreatic structure and endocrine and exocrine function.

Participants with and without prior wasting malnutrition, the SAMPA study primary exposure, will be compared within each cohort for all pancreas structure and function outcomes: diabetes by OGTT or HbA1c, exocrine function as indicated by faecal elastase and serum lipase, and pancreas size and presence of abnormalities detected by ultrasound or CT scan. We will initially fit regression models for each outcome with prior malnutrition as the main exposure, controlling for sex and for age as a continuous variable. We will investigate whether there are interactions between prior malnutrition and sex, which is known to be associated with both prior malnutrition and diabetes. We will then investigate whether the associations between malnutrition and the outcomes differ by the following variables:
•Time since malnutrition•Sitting/standing height ratio as an indicator of early life stunting•HIV status for African cohorts only (SAM Lusaka, NUSTART Lusaka, CICADA)

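### St-ATT: 17% of recruits already had HbA1c of 7.0% or more at the recruitment that supplies the BMI exposure, and the stated analysis cannot separate this from later dysglycaemia

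*Protocol article*

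**What the plan says.** **Exposure.** Table 1 (Study cohorts, cohort 5) states: "Between Aug 2018 and Feb 2020, the St-ATT cohort recruited 900 adults undergoing tuberculosis treatment in three provinces". The BMI distribution is given as "1-2 y prior: 900 total, 495 BMI >18.5 kg/m ^2^, 189 (21" per cent), with the remaining 216 (24%) below 17 kg/m². The size is "Expected for SAMPA: 600 total".

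**Glycaemia at recruitment.** The same entry says "17% had HbA1c >=7.0% (probable diabetes in TB) with an additional 30% with HbA1c 5.8%-7.0" per cent. It labels the upper band as probable diabetes in TB, and the lower band as prediabetes or mild hyperglycaemia induced by TB.

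**Outcome.** Under Assessments, the primary outcome for comparing people with and without prior malnutrition is "glucose ≥ 7.8 mmol/L at 2 hours in a standard OGTT". This is a state at the SAMPA visit, not a new onset.

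**Hypothesis and model.** Hypothesis 1 reads "Prior malnutrition is associated with later abnormal pancreatic structure and endocrine and exocrine function". Under Statistical analyses, regression models are first fitted "with prior malnutrition as the main exposure, controlling for sex and for age as a continuous variable". The section then examines a sex interaction, time since malnutrition, sitting/standing height ratio, HIV status (African cohorts only), and current BMI, fat mass index, fat-free mass index and diet pattern. Glycaemia at recruitment is not among these.

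**Eligibility.** The only ineligibility stated under Participant recruitment is refusal of both versions of the OGTT.

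**The concern.** To speak of a later abnormality, the analysis has to separate what followed the wasting from what was already there when wasting was recorded. In St-ATT the interval is only 1-2 years, and a sizeable minority were hyperglycaemic at its start. If they are still dysglycaemic at the SAMPA visit, they count as outcome events.

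Diabetes can itself influence BMI at recruitment. Diabetes accompanying overweight would place cases in the unexposed group. Uncontrolled diabetes with weight loss would place them in the exposed group. Controlling for sex and age addresses neither route.

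St-ATT is one of the two cohorts named as individually powered for this outcome, and primary analyses are by cohort, so pooling does not remove the difficulty.

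**Working it through.** **Inputs from the protocol article.** N = 600 expected; 495 of 900 (55%) with BMI above 18.5 and 405 of 900 (45%) below; 17% with HbA1c ≥7.0% at recruitment; planning scenario 7% v 14.5% with 80% power.

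**Assumptions.** Two-sided 5% test (not stated in the article). Exposure means BMI below 18.5. The 17% applies to the 600 who return. HbA1c and BMI belong to the same recruitment; this is inferred from the cohort description.

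**1. The plan's own power figure.** The groups are 0.55 × 600 = 330 and 0.45 × 600 = 270.
- Pooled prevalence = (330 × 0.07 + 270 × 0.145)/600 = 62.25/600 = 0.10375.
- SE under the null = √[0.10375 × 0.89625 × (1/330 + 1/270)] = 0.0250.
- SE under the alternative = √[0.07 × 0.93/330 + 0.145 × 0.855/270] = 0.0256.
- z = (0.075 − 1.96 × 0.0250)/0.0256 ≈ 1.01, so power is 84.4%.

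With a continuity correction, 80% power needs 586 participants in total, close to 600. The stated 80% is therefore reproduced.

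**2. Number already hyperglycaemic.** 0.17 × 600 = 102. The power scenario implies only about 62 outcome events in both groups together (23.1 + 39.15). If 50% to 100% of the earlier cases persist, they supply 51 to 102.

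**3. Possible bias when wasting has no effect.** Let r be the ratio of recruitment HbA1c ≥7.0% in the wasted to that in the others, and f the share of those cases that persist. Assume everyone else has a 7% risk of dysglycaemia at SAMPA in both groups.
- Prevalence in the unexposed: p_u = 0.17/(0.55 + 0.45r). In the exposed: p_e = r × p_u.
- Spurious difference = f × (p_e − p_u) × (1 − 0.07).

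| r (assumed) | p_e | p_u | f = 0.5 | f = 1 |
|---|---|---|---|---|
| 2 | 23.4% | 11.7% | +5.5 points | +10.9 points |
| 1 | 17.0% | 17.0% | 0 | 0 |
| 0.5 | 11.0% | 21.9% | −5.1 points | −10.2 points |

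**4. Possible distortion of a real effect.** Keep the same set-up, but with true risks of 14.5% v 7% among the rest. The observed difference is then:
- r = 2: 12.1 to 16.6 points;
- r = 1: 6.9 to 6.2 points;
- r = 0.5: +2.0 to −3.5 points.

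Each range runs from f = 0.5 to f = 1. The true 7.5 points can be inflated, slightly diluted or reversed.

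**5. Power of a restricted estimate.** 0.83 × 600 = 498, split 274/224 if earlier cases are equally common in both groups. The formula in step 1 gives 77.4%, and the difference detectable at 80% power is 7.8 points. If exposure meant BMI below 17 against all others, power would fall from 75.6% to 68.5%.

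**The case against.** **The design is declared as it is.** The Introduction describes cross-sectional investigations in recalled cohorts, the hypothesis is worded as an association, and Table 1 assigns the longitudinal components to CICADA. A comparison of people free of hyperglycaemia at recruitment is therefore a different estimand, not the repair of a mistake. This stands, and it is why the all-participant estimate should be kept. It does not license reading that estimate as a later effect.

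**Sex and age are only the initial model.** Current BMI, fat mass and diet are examined afterwards, and insulin modelling and autoantibodies help to distinguish types of diabetes. True, but none of these shows whether dysglycaemia was present when BMI was recorded. Further sensitivity analyses may sit in a fuller document, and the St-ATT flow chart is not shown. The visible text states none.

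**Some of the early hyperglycaemia may be transient, and HbA1c is a different test from the OGTT.** Correct. The persistence range allows for this.

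**Restriction can itself mislead.** Wasting before TB recruitment may already have raised HbA1c. Restricting on HbA1c, or adjusting for it, could then remove part of a true early effect. This stands, and it argues against making the restricted estimate the main one.

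**Stronger readings that the article does not support.**
- A reader might infer that old diabetes inflates the St-ATT effect. HbA1c by BMI group is not given, so the bias may be positive, negative or zero.
- A reader might infer that most St-ATT events will predate follow-up. The share is 0.17f/(0.17f + 0.83i), where i is the assumed rate of new dysglycaemia. It is 56% to 91% for f = 0.5, i = 0.08 to f = 1, i = 0.02. It is only 34% to 41% for f = 0.5 with i = 0.20 to 0.15. With a further 30% in the intermediate HbA1c band, the higher rates are plausible.
- A reader might extend the point to all of CICADA, since "CICADA has the most detailed longitudinal diabetes data of the project cohorts, archived fasting samples". For members whose exposure dates from 16 or 11 years earlier, the article documents no glycaemia at that visit. The point is plausible only for the subgroup recruited 3-4 years ago with diabetes assessment among its purposes.

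**Conclusion.** The point holds for St-ATT in a limited form. As described, the Hypothesis 1 analysis lets dysglycaemia that predates or coincides with the exposure measurement enter an outcome presented as later. About 102 of 600 participants are concerned if the 17% carries over to those who return. Under the assumed two-fold imbalances the distortion is as large as the 7.5-point target, in either direction; with no imbalance there is no spurious effect.

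What is established is that the stated analysis cannot tell these situations apart. It is not established that the St-ATT estimate is biased, or in which direction. The conclusion rests on BMI and HbA1c coming from the same recruitment. It is a worthwhile, inexpensive improvement rather than a fatal flaw.

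**What to change.** - Keep the all-participant St-ATT estimate for 2-hour glucose as planned.
- Pre-specify beside it the same model restricted to participants with HbA1c below 7.0% at recruitment.
- State that a St-ATT association will not be attributed to later effects of wasting unless it is also seen in the restricted estimate.
- Tabulate recruitment HbA1c by BMI group. This would show whether the imbalance exists and in which direction.
- Do the same for the CICADA subgroup recruited 3-4 years ago, if glycaemia was recorded at the visit that defined exposure.

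**Cost.** This needs analysis wording and one extra model; Table 1 shows that the St-ATT recruitment HbA1c exists. The restricted estimate uses about 498 participants, with power for 7% v 14.5% of about 77% instead of 84% (two-sided 5% assumed, no continuity correction). It may also remove part of an early effect of wasting, which is why both estimates should be reported.

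### In CLHNS, low birth weight is recorded, comes before the wasting exposure and is treated by the protocol as a cause of later disease, yet the stated Hypothesis 1 model does not name it as a covariate

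*Protocol article*

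**What the plan says.** **Cohort.** Table 1 describes CLHNS as a birth cohort: "All singleton births were included regardless of nutrition status". The SAMPA sample and exposure are "of 420 total to be included, 143 (34%) WHZ<-3", measured up to age 2 years. LBW status is given for the wasted group only: "28 LBW of the 143 with childhood malnutrition".

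**Role of birth weight.** The Introduction states that "prenatal malnutrition, usually measured as low birth weight, can increase the risk of NCDs in later life". Table 1 makes the Indian cohort (DIVIDS), all born LBW, a positive control because "we expect adverse long-term non-communicable disease consequences of being born LBW".

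**Model.** Under Statistical analyses and sample size calculations, "Primary analyses will be conducted for each cohort separately". The Hypothesis 1 models are first fitted "controlling for sex and for age as a continuous variable". Effect modification is then examined by sex, time since malnutrition, HIV status (African cohorts) and "Sitting/standing height ratio as an indicator of early life stunting". Current BMI, fat and fat-free mass indices and diet pattern are discussed as possible mediators or modifiers. Birth weight is in none of these lists, nor among the modifiers given under Figure 1.

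**The concern.** A variable that precedes the exposure, may be associated with it and affects the outcome is a candidate confounder. In CLHNS birth weight meets the first and third conditions on the protocol's own account, and its status is already recorded. It cannot be a consequence of later wasting, so the caution the article rightly applies to current BMI and fat mass does not apply here.

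The named adjusters do little in this cohort. The mothers were enrolled while pregnant in 1983-84, so participants are almost the same age, and the stated model in effect adjusts for sex alone. The sitting/standing height ratio does not fill the gap: it is a proxy for stunting and is used to test interaction, not to adjust.

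Two uses of the CLHNS result are exposed. It is the cohort presented as having the longest interval since anthropometrically defined malnutrition. It is also, by Table 1, the only adult cohort whose exposure is defined in early childhood, so in the planned pooled analyses a prenatal contribution there could be read as an effect of age at malnutrition.

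**Working it through.** **Inputs from the article.** CLHNS total 420; wasted 143; LBW among the wasted 28 (Table 1). Prevalence of 2-hour glucose of at least 7.8 mmol/L without malnutrition: 7%, a planning value used for CICADA and St-ATT and carried over to CLHNS here as an assumption. Planning differences: 7.5 percentage points (CICADA and St-ATT) and 0.4 SD.

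**Inputs assumed.** LBW rate in the unexposed, p0: 5% to 15%, plus the case of equality. Risk ratio of LBW for the outcome, RR: 1.5 to 3. LBW effect on continuous outcomes: 0.2 to 0.5 SD. Two-sided alpha 0.05.

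**1. The article's figure.** 143/420 = 34.0%, as stated. Unexposed: 420 - 143 = 277. LBW among the wasted: p1 = 28/143 = 19.6%.

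**2. Bias in the risk ratio when LBW is left out.**

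B = [1 + p1(RR - 1)] / [1 + p0(RR - 1)]

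If wasting has no effect, the spurious excess is 7% × (B - 1).

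| p0 | RR 1.5 | RR 2 | RR 3 |
|---|---|---|---|
| 5% | 1.07 (+0.50 points) | 1.14 (+0.97) | 1.27 (+1.86) |
| 10% | 1.05 (+0.32) | 1.09 (+0.61) | 1.16 (+1.12) |
| 15% | 1.02 (+0.15) | 1.04 (+0.28) | 1.07 (+0.49) |
| 19.6% | 1.00 (0) | 1.00 (0) | 1.00 (0) |

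Largest case: (1 + 0.196 × 2)/(1 + 0.05 × 2) = 1.392/1.10 = 1.265, and 7% × 0.265 = 1.86 points. Above p0 = 19.6% the sign would reverse.

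**3. Continuous outcomes.** Bias = (p1 - p0) × LBW effect. At p0 = 5%: 0.146 × 0.2 to 0.5 = 0.03 to 0.07 SD. At p0 = 10%: 0.096 × 0.2 to 0.5 = 0.02 to 0.05 SD.

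**4. Scale.** The largest case is 1.86/7.5 = 25% of the planning difference, and 1.86/3 = 62% of the smallest difference (3 points) that the article cites from other studies. The standard error of a risk difference in CLHNS at 7% is √[0.07 × 0.93 × (1/143 + 1/277)] = 2.6 points.

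**5. Cost of adjusting.** Power for 0.4 SD with 143 versus 277 is 97.3% unadjusted. Regressing exposure on LBW gives R² = 0.053 at p0 = 5%, so the variance inflation is 1/(1 - 0.053) = 1.056 and power is 96.6%. At p0 = 10% it is 97.1%, and at 19.6% it is 97.3%. Any gain from explained outcome variance is not counted.

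**The case against.** **The covariate list may not be closed.** The sex-and-age model is called the initial one, the analyses are to follow a conceptual framework whose figure is not shown, and socioeconomic terciles are derived for analysis without appearing in that model. This is an article, and a fuller plan may add birth weight. That stands: the accurate statement is that birth weight is not named, not that adjustment is ruled out. The point survives because the article does name its adjusters and modifiers and reasons at length about the causal role of other variables, but passes over the one pre-exposure factor it treats as causal elsewhere.

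**Bias is not shown.** A reader might infer that prenatal effects are in fact being credited to wasting. The documents do not support this: LBW is given only for the 143 wasted participants, how the 420 were chosen is not in the text, and the assumed rates and risk ratios are not the article's. Even in the largest case the bias is below one standard error of the CLHNS risk difference. This stands and limits the claim to a possibility.

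**Separating prenatal from postnatal effects is not a stated objective.** Correct: the objectives concern wasting at any age, and prenatal growth is background. But an effect attributed to wasting should still be free of a known earlier cause.

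**Timing.** The text does not say whether measurements at birth count towards the exposure. If they do, birth weight overlaps with it in part. For wasting after birth the order is clear.

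**Conclusion.** The point holds for CLHNS in a limited form. As written, the Hypothesis 1 model leaves out a recorded, pre-exposure variable that the protocol regards as raising later disease risk, so the CLHNS estimate may combine prenatal growth effects with those of wasting. Whether it does depends on the LBW rate in the 277 unexposed participants. If that is also 19.6%, there is no bias; with 5% to 15% and an LBW risk ratio of 1.5 to 3, the excess is about 0.15 to 1.9 percentage points on a 7% base. Bias of that size could not by itself produce the planned differences of 7.5 points or 0.4 SD, but it could distort smaller ones.

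A reader might extend the point to DIVIDS, because weight still varies below 2.5 kg. The CLHNS argument and calculation do not carry over: every DIVIDS participant was born LBW, and the article gives nothing on how birth weight differs by later wasting there. Adjustment in that cohort is optional.

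**What to change.** In the CLHNS Hypothesis 1 models, name birth weight as a pre-exposure covariate alongside sex and age: continuous if it is available for all 420, otherwise LBW yes/no. The article shows LBW status only for the wasted group, so availability for the other 277 must be confirmed. Report the LBW rate in those 277. Present estimates with and without birth weight in the same participants, so that a change reflects the covariate and not a change of sample. State whether measurements at birth count towards the wasting exposure.

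The cost is one covariate, less than one percentage point of power at 0.4 SD (97.3% to 96.6% at worst over the range examined), and the loss of any participant without a recorded birth weight.
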